### Procedures

2.6

The Wellbeing Neuro Course will be employed as the intervention in this study and is a digital psychological treatment for adults with neurological disorders.^31^ This intervention has been carefully developed to be suitable for adults with a broad range of neurological disorders, including PWE. It uses the principles of both cognitive behavior therapy and compensatory cognitive rehabilitation to target several domains of mental health and functional disability and covers a range of skills for managing depression, anxiety, cognitive difficulties, and activity/fatigue levels. A comprehensive overview of the intervention has been previously reported.^31^ A previous RCT of the intervention in a guided format found significant benefits on measures of depression, anxiety, disability, and cognitive function in the treatment group relative to the TAU‐WLC.^32^ Participants included a mixed sample of PWE, MS, Parkinson's disease, or an acquired brain injury. Acceptability of the treatment was also high, with over 90% of participants reporting that the course was worth their time and that they would recommend it to others.

The course includes six online lessons which are provided over a 10‐week period. Participants will work through the course according to a predetermined timetable and cannot access new materials without first having read previous materials. The course also includes worksheets for each lesson, additional written resources that can be downloaded, and case stories based on previous participants which can be followed throughout the course.

Participants allocated to the guided group will have access to support from an eCentreClinic clinician as they work through the course. All clinicians will be mental health professionals and will be employed by Macquarie University or one of its entities (e.g., MQ Health). All mental health professionals will be provided with training and supervision from a senior clinical psychologist to ensure competence and safety in their practice.

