### Power and sample size

2.9

Sample size was determined in line with expert guidelines^43^ and calculations included data from a previous RCT, which observed a standard rate of symptom change on our primary outcomes of depression and anxiety of 24% each.^32^ We utilized specialized longitudinal software^44^ to account for our proposed generalized estimation equations models (GEE). Power analyses were conducted with Type I error set at α = 0.05 and Type II error at β = 80% and utilized a DELTA2 methodology.^43^

Our superiority analyses will compare the two active treatment groups with the TAU‐WLC. We calculated that this requires a sample size of 125:80 (e.g., unguided: control) to detect a difference in the rate of symptom change as small as 11% on the mental health primary outcomes from baseline to post‐treatment.^44^ Our noninferiority analyses will compare the unguided and guided treatment groups. In line with power estimation for non‐inferiority thresholds^44^ in mental health trials,^45^, ^46^ we considered a difference of 50% of the standard rate of symptom reduction in depression and anxiety symptoms (i.e., 12% reduction in symptoms at post‐treatment) as the prespecified margin of noninferiority.^47^ Based on these margins, we require a sample size of 125:125 (unguided: guided).

Utilizing a conservative attrition estimate of 20%, a final larger sample of 150:150:75 (“Guided: Unguided” control) was decided.

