### Clinical efficacy

3.1

We will report clinical efficacy findings with and without data imputations under the intention‐to‐treat analysis and missing data assumptions (e.g., completer's analysis). The intention‐to‐treat approach will involve all outcomes being evaluated and imputed for all participants who were randomized and provide baseline data, consistent with previous research.^32^, ^46^

Clinical efficacy will be assessed utilizing longitudinal GEE models to assess changes in the primary and secondary clinical outcomes over time and between the three groups.

Post‐treatment is the primary endpoint for changes in the primary and secondary clinical outcomes. To determine whether post‐treatment improvements are maintained over time, within‐group time effects will be examined at 3‐ and 12‐month follow‐ups. For all analyses, the level of statistical significance will be set at alpha 0.05. All GEE models will include log‐link function and gamma scale parameters to account for the positive skew in the clinical outcome data.

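### The 12% non-inferiority margin is larger than the 11% superiority target, and the non-inferiority claim does not depend on unguided care beating control

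*Protocol article*

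**What the plan says.** All references are to the protocol article.

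- **Margin (2.9 Power and sample size).** The margin is "a difference of 50% of the standard rate of symptom reduction in depression and anxiety symptoms", spelled out as 12% at post-treatment. The reference rate is 24% for both depression and anxiety and comes from an earlier RCT. The section does not say whether 24% is a within-group change or a difference from control.
- **Source of the 24% (2.6 Procedures).** The same citation is described there: "A previous RCT of the intervention in a guided format found significant benefits". Its sample mixed epilepsy, MS, Parkinson's disease and acquired brain injury.
- **Superiority (2.9).** The comparison of each active arm with TAU-WLC needs 125:80 "to detect a difference in the rate of symptom change as small as 11" per cent.
- **Non-inferiority sample size (2.9).** 125:125, unguided to guided.
- **Hypotheses (1 Introduction).** Both active arms beating TAU-WLC, and non-inferiority between the two active arms, are listed as separate hypotheses. Neither is made a condition of the other.
- **Analysis (3.1 Clinical efficacy).** "All GEE models will include log‐link function and gamma scale parameters", and "For all analyses, the level of statistical significance will be set at alpha 0.05". No order of testing is given for the superiority and non-inferiority comparisons.

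**The concern.** A non-inferiority result for unguided care is useful only if the guided arm's benefit in this trial clearly exceeds the margin. Section 2.9 counts an 11% difference from control as worth detecting, yet its margin for a loss between the active arms is 12%. A guided benefit at the bottom of the range the trial is powered for would be smaller than the margin, so excluding a loss of 12 points would not exclude a complete loss of benefit.

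The protection must then come from one of two places. One is confidence that the guided effect here is near 24%. That figure rests on an earlier trial in a mixed sample and is not identified as an effect against control. The other is a rule that unguided must itself beat TAU-WLC. The control arm for such a rule is being enrolled, but the rule is not stated.

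The stakes are practical. Non-inferiority together with lower cost is the argument for unguided care (third hypothesis in the Introduction), and section 3.5 plans a budget-impact analysis of scaling up the most cost-effective version. Section 1 also warns that people with complex presentations, including epilepsy, may not do well without clinician support, so a weak unguided effect is a risk the protocol itself recognises.

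**Working it through.** **1. The plan's own figure.** Margin = 0.5 × 24% = 12%, which reproduces. I read it as 12 points of percentage improvement from baseline.

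**2. What the margin leaves.** Benefit of unguided over control at the margin = guided benefit − 12. The premise in 2.6.1 Randomization is that control does not improve.

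| True guided benefit (points) | Left at the margin | Share retained |
|---|---|---|
| 24 | 12 | 50% |
| 18 | 6 | 33% |
| 15 | 3 | 20% |
| 12 | 0 | 0% |
| 11 | −1 | none |

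**3. Back-solving the SD (assumption).** No SD or within-person correlation is given, so 125:125 cannot be reproduced. I use the "Type I error set at α = 0.05" of section 2.9 as two-sided (one-sided 0.025 for non-inferiority). I read "Type II error at β = 80" per cent as 80% power. With a normal approximation, SD = difference / [(z_α + z_power) × √(1/n1 + 1/n2)]:

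- Superiority, 125:80, 11 points: 11 / (2.802 × 0.1432) = 27.4.
- Non-inferiority, 125:125, 12 points, true difference 0, one-sided 0.025: 12 / (2.802 × 0.1265) = 33.9.
- The same at one-sided 0.05: 12 / (2.486 × 0.1265) = 38.2.

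The first two SDs differ, but an assumed true shortfall of about 2.3 points would reconcile them (12 − 2.802 × 0.1265 × 27.4 = 2.3). The sample size is therefore not shown to be wrong, and I carry the range 27.4 to 38.2.

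**4. Chance of declaring non-inferiority when unguided is inert.** SE = SD × √(2/125), which is 3.47, 4.28 and 4.83 for the three SDs. With d the true guided benefit, P = Φ((12 − d)/SE − 1.96). The figures below are from 400,000 simulated trials per setting and agree with the formula.

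| d (points) | SD 27.4 | SD 33.9 | SD 38.2 |
|---|---|---|---|
| 24 | 0.000 | 0.000 | 0.000 |
| 18 | <0.001 | <0.001 | <0.001 |
| 12 | 0.025 | 0.025 | 0.025 |
| 11 | 0.048 | 0.042 | 0.040 |
| 6 | 0.41 | 0.29 | 0.24 |
| 0 (neither works) | 0.93 | 0.80 | 0.70 |

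**5. The same, if unguided must also beat TAU-WLC (125:80, two-sided 0.05).** The joint probability cannot exceed the 0.025 chance that an inert arm beats control. Simulated values are about 0.024 at d = 0, 0.016 to 0.021 at d = 6, and 0.005 to 0.006 at d = 11.

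**6. What the condition costs in power.** With 20% attrition, 150:75 leaves 120:60, and SE = SD × √(1/120 + 1/60) = SD × 0.158, or 4.34 to 6.03.

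- Unguided truly 24 points better than control: Φ(24/6.03 − 1.96) = Φ(2.02) = 0.98 at the largest SD, and higher at the others.
- Unguided truly 11 points better: Φ(11/4.34 − 1.96) = 0.72 at SD 27.4, falling to Φ(11/6.03 − 1.96) = 0.45 at SD 38.2.

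**The case against.** A reader might infer that, because 12 exceeds 11, the margin by itself lets an ineffective course pass as non-inferior. The document does not support that. The 11% is the smallest difference the superiority test is sized to detect, not the expected effect. The margin derives from the 24% reference, and if that holds and control does not improve, it preserves half the effect and an inert unguided arm practically never passes. The margin is also not the pass mark: at SE 4.28 the observed shortfall must be below 12 − 1.96 × 4.28 = 3.6 points, and a true 12-point shortfall passes only 2.5% of the time. All of this stands.

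It is also fair that both active arms are to be compared with TAU-WLC, so a report in which neither works would show failed superiority beside the non-inferiority result. If neither arm works, the statement that unguided is no worse than guided is literally true. A formal testing order is something an article may leave to the analysis plan. This lowers the severity. It does not remove the point, because the margin and the hypotheses are fixed here and, as written, the second hypothesis can be called supported whatever happens to the first.

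Two further inferences fail. One is that a log-link model cannot carry a percentage margin. It yields ratios, and section 3.2 Clinical significance derives percentage improvement from the model's marginal means. A fixed ratio of 0.88/0.76 = 1.158 would equal 12 points only at a guided reduction of exactly 24%; at 40% it is 0.158 × 60 = 9.5 points. The other is that "the level of statistical significance will be set at alpha 0.05" means a one-sided 0.05 non-inferiority test. The text does not say so, and the analysis plan may settle it.

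That the effect in epilepsy will be smaller than 24% is conjecture: the earlier sample included people with epilepsy, and the effect could equally be larger.

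**Conclusion.** The concern holds in a limited form. The margin exceeds the superiority target, its 24% basis is not identified as an effect against control, and the non-inferiority conclusion is not conditioned on superiority over TAU-WLC. This matters only if the guided benefit in this trial is near or below 12 points. For an inert unguided arm the chance of a non-inferiority claim is then about 4-5% at 11 points, against a nominal 2.5%. It rises to 24-41% at 6 points and 70-93% if guided fails too. At a guided benefit of 18 points or more it is below 0.1%.

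These figures are per outcome. They rest on an SD back-solved from the stated sample sizes, a normal approximation in points of baseline, 125 analysed per arm and a one-sided level of 0.025. I treat this as an inexpensive improvement to how the claim is framed, not as an error that invalidates the design or its sample size.

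**What to change.** In sections 2.9 and 3.1, or in the analysis plan before data are examined:

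1. State that non-inferiority on a primary outcome will be claimed only if unguided is first superior to TAU-WLC on that same outcome.
2. Report, with confidence intervals, the unguided-versus-control effect and the share of the guided effect retained. The share will be unstable if the guided effect is small, so it should sit beside the absolute effect.
3. State openly that the 12% margin exceeds the 11% superiority target, and say whether the 24% reference is a within-group change or a difference from control.
4. If the margin is to be tested on the percentage-improvement scale of section 3.2, say so.

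This needs wording only: no added participants, visits or measures. The price is that the claim becomes harder to make when superiority fails. That price is small if unguided achieves something like 24 points (superiority power about 98% or more at 120:60), and real if its benefit is only about 11 points (about 45-72%).

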Meta‐analytic evidence in the general population, and for those with chronic pain, suggests that on average guided interventions are more clinically efficacious than unguided interventions.^27^, ^28^ In contrast, unguided models have greater public health potential, as they cost less, are easier to implement in routine care settings, and have been found to be efficacious for mild/subthreshold depression.^28^ Yet, participants with severe or complex mental health presentations, such as those with neurological comorbidities including epilepsy, may not achieve good clinical outcomes without clinician support.

Thus, the comparative clinical and cost‐effectiveness of guided and unguided digital interventions remains an important topical area of investigation^15^ and critical information to inform healthcare service providers. Reflecting this, a carefully developed digital chronic pain management intervention was similarly clinically efficacious and acceptable in an unguided and guided model; however, the unguided model was more cost‐effective.^29^ This research highlights the importance of comparative effectiveness trials to inform decision‐makers about the relative merits of different models of care. One recent randomized controlled trial (RCT) in adults with MS compared the efficacy of a digital cognitive behavior‐based program in a guided or unguided format with a treatment‐as‐usual, waitlist, control group.^22^ Both versions of the program led to a significant reduction in depression symptoms compared to the control group. However, a direct comparison between the guided and unguided groups was not performed. To date, there have been two RCTs of digital psychological interventions in epilepsy, both of which utilized unguided models of care.^24^, ^25^ Notably, while both reported that the treatment arms experienced significant improvements in symptoms of depression compared to controls, they also experienced relatively high dropout rates (>25%). On the other hand, an open trial of a guided digital psychological intervention to improve mental health in PWE observed very low rates of attrition (4%).^30^ These findings highlight potential differences in intervention engagement based on levels of guidance. However, conclusions in this area can only be reached following clinical trials that directly compare these different care models.

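### After the plan's own 20% attrition, 150:150:75 leaves 120:120:60: power for the 11% superiority difference is about 72%, not 80%, while non-inferiority is only slightly short

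*Protocol article*

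**What the plan says.** All the sample-size figures are in section 2.9, Power and sample size, of the protocol article.

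- Error rates: "Type I error set at α = 0.05 and Type II error at β = 80"%.
- Superiority, active arm against the waiting-list control: "We calculated that this requires a sample size of 125:80 (e.g., unguided: control) to detect a difference in the rate of symptom change", with 11% as the smallest difference targeted.
- Non-inferiority, with a margin of 12% (half of the 24% change seen in the earlier trial): "Based on these margins, we require a sample size of 125:125 (unguided: guided").
- Final size: "Utilizing a conservative attrition estimate of 20%, a final larger sample of 150:150:75".

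Sections 2.1, 2.2 and 2.6.1 confirm a ceiling of 375, arms of 150, 150 and 75, and 2:2:1 allocation in blocks of 10, so 75 is not a misprint. Section 2.6.1 explains the lighter control weighting by economy of recruitment. It does not say why the control number is below the 80 in section 2.9, or how attrition in that arm was allowed for.

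On dropout, the Introduction says of the two earlier unguided digital trials in epilepsy that "they also experienced relatively high dropout rates (>25"%). It also reports 4% attrition in an open trial of a guided programme.

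**The concern.** Section 2.9 presents the final sample as the required sample enlarged for 20% attrition. The four figures (125:80, 125:125, 20%, 150:150:75) do not fit together on that account, and the gap is widest in the control arm, which limits both superiority contrasts. Superiority of each active arm over control on depression and anxiety is the first hypothesis. A reader will take it that the trial keeps 80% power for an 11% difference after a fifth of participants are lost. By the plan's own numbers it does not.

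The β statement adds a smaller problem: read literally, "Type II error at β = 80"% means 20% power. The intended meaning is clear, but the sentence is wrong.

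**Working it through.** **Inputs (section 2.9).** Required n 125:80 and 125:125; α = 0.05; power 80% (the intended reading of the β statement); superiority difference 11%; non-inferiority margin 12%; attrition 20%; final n 150:150:75.

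**Step 1. Can the final sample be reproduced?**

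| Rule | Active (from 125) | Control (from 80) |
|---|---|---|
| n / (1 − 0.20) | 156.25, so 157 | 100 |
| n × 1.20 | 150 | 96 |
| Plan | 150 | 75 |

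The active arms match the n × 1.20 shortcut, which does not fully offset a 20% loss. Neither rule gives 75 controls.

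**Step 2. What remains after 20% attrition?** 150 × 0.8 = 120 and 75 × 0.8 = 60, so 120:120:60. The shortfalls are 5, 5 and 20.

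**Step 3. Power for superiority.** The base figure of 125:80 cannot be re-derived, because SD, correlation and sidedness are not given. I therefore take the plan at its word that 125:80 gives 80% power and scale from there. Two-sided, the noncentrality at 125:80 is 1.960 + 0.842 = 2.802. It scales with the inverse of SE factor = √(1/n₁ + 1/n₂), and power = Φ(noncentrality − 1.960).

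| n (active:control) | SE factor | Noncentrality | Power for 11% | Difference detectable with 80% power |
|---|---|---|---|---|
| 125:80 (required) | 0.1432 | 2.802 | 80% | 11% |
| 150:75 (no loss) | 0.1414 | 2.836 | 81.0% | 10.9% |
| 120:60 (20% loss) | 0.1581 | 2.537 | 71.8% | 11 × 0.1581/0.1432 = 12.1% |

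With one-sided α = 0.05, power at 120:60 is 72.8%. The detectable difference is unchanged.

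**Step 4. How much attrition can the contrasts absorb?** The information measure 1/(1/n₁ + 1/n₂) is 48.8 at 125:80, 50.0 at 150:75 and 40.0 at 120:60. Equal attrition in both arms brings 150:75 down to the requirement at 1 − 48.8/50.0, about 2.4%. Non-inferiority reaches 125 per arm at 1 − 125/150 = 16.7%.

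**Step 5. Non-inferiority.** At 120:120 the noncentrality is 2.802 × √(120/125) = 2.745, so power is 78.4% (78.6% with one-sided 0.05).

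**Step 6. Higher attrition in the unguided arm.** Take 25% there, as an illustration from the Introduction, and 20% elsewhere, so 112.5 unguided remain.

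- Superiority, 112.5:60: SE factor √(1/112.5 + 1/60) = 0.1599; power about 71%; detectable difference about 12.3%.
- Non-inferiority, 112.5:120: 1/112.5 + 1/120 = 0.0172 against 2/125 = 0.0160; power about 77%.
- Non-inferiority with 25% unguided and 4% guided, 112.5:144: 1/112.5 + 1/144 = 0.0158; power about 80%.

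**The case against.** **The trial is not short of power for the effect it expects.** The 11% is the smallest difference targeted. Section 2.9 cites a 24% change in the earlier trial and section 2.6.1 says controls did not improve. If the true difference were 24%, the noncentrality at 120:60 would be 2.537 × 24/11 = 5.5 and power would exceed 99%. This stands. A reader might infer that the trial is underpowered or must recruit more, and the documents do not support that. The defect is in a stated property of the design.

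**The control number alone costs nothing.** It is tempting to say that power is lost because 75 is below 80. It is not: 150:75 carries slightly more information than 125:80. The loss appears only once the stated attrition is applied. Nor is the word *larger* false overall, since 375 exceeds 125 + 125 + 80 = 330 and both active arms grew. Only the control arm did not.

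**Non-inferiority is barely affected.** This stands. The loss is under 2 points at 20% attrition. Putting 25% on both active arms would overstate it, because the Introduction's 4% comes from a guided programme; with 25% and 4% by arm there is no shortfall.

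**20% may be fair as a single figure.** It lies between 4% and more than 25%. The Introduction also says that unguided models with an interview lose fewer people than fully automated ones, and this trial includes an interview. So *conservative* is not shown to be wrong across the trial. For the unguided arm, it is unsupported against the dropout the article itself cites.

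**Imputation keeps everyone in the analysis.** Sections 3.1 and 3.4 impute for all randomised participants with baseline data. That retains the headcount but does not restore unobserved post-treatment information, and section 2.9 itself treats attrition as a loss to be allowed for. Partial recovery is possible, which is one reason to treat 72% as approximate.

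**Pooling the active arms** (240:60) would give about 79%. But section 2.9 sizes a single active arm against control, and the first hypothesis concerns both groups.

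**Conclusion.** The point holds for superiority. With the plan's own requirement and attrition, 150:150:75 leaves 120:120:60. The headcount mismatch needs no assumption. The stated 80% power for an 11% difference becomes about 72%; equivalently, the difference detectable with 80% power is about 12.1%. Non-inferiority falls only to about 78%.

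The power figures rest on a normal approximation, on calibration to exactly 80% at 125:80 and 125:125, and on dropouts contributing no post-treatment information. They do not come from the longitudinal GEE software the plan used. The β wording is an error of labelling and does not show that the calculation used 20% power.

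**What to change.** Keep 375 participants and revise section 2.9:

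1. Rerun the power in the trial's longitudinal GEE software at 120:120:60 and report it with the detectable difference. Expect about 72% for an 11% superiority difference (80% for about 12.1%) and about 78% at the 12% non-inferiority margin. Print the rerun values, not these approximations.
2. State that the control arm was not inflated for attrition.
3. Replace the Type II error statement with: power 80% (β = 20%).
4. Either justify calling 20% conservative for the unguided arm, given the dropout above 25% cited in the Introduction, or add a sensitivity figure with higher attrition in that arm. At 25% there and 20% elsewhere, expect about 71% for superiority and 77% for non-inferiority.

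The cost is one software rerun, a few sentences and a slightly less favourable stated figure. Enlarging the trial is not proposed. For scale, matching the information of 125:80 at 2:2:1 after 20% attrition would take about 148:74 analysable, that is 148/0.8 = 185 and 74/0.8 = 92.5, so about 185:185:93 or 463 in total.
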